## 6. Analysis

### 6.1. Outcome definitions, measurement and calculation

#### 6.1.1. Primary outcomes

The primary endpoint [2] is the proportion of patients with a clinical response to therapy 14-16 weeks after initiation of treatment with a biological agent. Thus, the primary outcome will be a composite depending on the disease specific definitions of clinical response, defined below:

- CD/Crohn's disease: clinical remission, defined as Harvey-Bradshaw Index (HBI) of 4 or less [25].
- UC/Ulcerative colitis: clinical remission, defined as Mayo Clinic Score of 2 or less (with no individual subscore of >1) [26-28].
- RA/Rheumatoid arthritis: clinical response, defined as at least a 20% improvement according to the criteria of the American College of Rheumatology (ACR20) [29, 30].
- AxSpA/Axial spondyloarthritis: clinical response, defined as at least a 20% improvement according to the Assessment of Spondyloarthritis International Society (ASAS20) [31, 32].
- PsA/Psoriatic arthritis: clinical response, defined as at least a 20% improvement according to the criteria of ACR20 [33].
- PsO/Psoriasis: clinical response, defined as at least a 75% improvement in the Psoriasis Area and Severity Index (PASI 75) [34].

For the measurement and calculation of HBI, Mayo Clinic Score and PASI see table A. ACR20 and ASAS20 are composite outcome measures defined below with composites further explained in table A.

ACR20 is a composite measure developed by the American College of Rheumatology for assessment of improvement of RA patients in clinical trials [30] but also used for assessment of PsA [33]. ACR20 is defined as  $\geq 20\%$  improvement in tender and swollen joint counts and  $\geq 20\%$  improvement in at least three out of the following five measures: 1) pain, 2) patient global assessment, 3) physician global assessment, 4) self-assessed

physical disability and 5) CRP or erythrocyte sedimentation rate. Information for calculation of ACR20 will be extracted from the Simplified Disease Activity Index (SDAI; patients and physicians global assessment and tender and swollen joint count) and the Health Assessment Questionnaire Disability Index (HAQ-DI; disability, see table A), while pain is a separate question in the self-administered questionnaire ("how much pain due to your arthritis do you suffer from, the past two days?") on a VAS 0-100 mm.

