| (DAS)28-CRP: Disease Activity Score                                                                           | DAS28-CRP is a composite measure of disease activity in RA ranging on a scale from 0 to 9.4 [41] [42]. It is calculated using 4 variables (swollen and tender joint counts (SJC and TJC, 0-28), CRP (mg/L) and patient global assessment (PGA, 0-100 mm VAS))[41]:
$DAS28(CRP) = \sqrt{TJC} + 0.28 * \sqrt{SJC} + 0.36 * \ln(CRP + 1) + 0.014 * PGA + 0.96$                                                                                                                                                                                                                                                                                                                                                                                                                                                           | RA
PsA  |
| SDAI:
Simplified Disease Activity Index

- Tender and Swollen joints
-Patient's Global Assessment | SDAI is also a composite measure for monitoring disease activity in RA. The index includes five clinical measures: swollen and tender joint count (0-28), patient global assessment of disease activity (10 cm VAS), provider global assessment of disease activity (10 cm VAS), and CRP (mg/dl). The sum of the five items is the SDAI score [42].
Tender and swollen joint counts + Patient's and Physician's Global Assessment are composites in ACR20.                                                                                                                                                                                                                                                                                                                                                            | RA
PsA  |

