| PASI score                                                                                                    | PASI is a standard scoring tool used to measure the severity and extent of psoriasis ranging from 0 to 72. The four main body areas (the head: 10% of total body, the trunk: 20%, the upper extremities: 30% and the lower extremities: 40%) are each evaluated for area of psoriatic involvement with a numerical value from 0-6 corresponding to percentages of involvement in that area [45]. Next, the severity of the psoriatic lesions is evaluated for each body on three factors (erythema, infiltration and desquamation) on a scale from 0-4. For calculation of the PASI [45], for each body area, the sum of severity for these three factors are multiplied with the numerical value of involvement and the percentage of the total body. The sum of the values for the four body areas are the PASI score. | Pso
PsA |
| DLQI:
Dermatology Life Quality Index                                                                       | DLQI is the most frequently used dermatology-specific measure of life quality in clinical trials of skin diseases [46]. It is composed of ten questions concerning the impact of the respondents' skin on different aspects of quality of life over the past week. Each item in the DLQI is scored on a 4-point scale (not relevant/not at all= 0, a little=1, a lot= 2, very much= 3), and the sum of the ten items is the total score (0-30) [46].                                                                                                                                                                                                                                                                                                                                                                     | PsO        |

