| ΔSCCAI, score (0-19)                                                                                                                                                                                                                                                                                                                                                                                                                                                                                                                                                                                                                                               |         |      |         |      |                     |
| ΔSDAI, score (0-86)                                                                                                                                                                                                                                                                                                                                                                                                                                                                                                                                                                                                                                                |         |      |         |      |                     |
| ΔSwollen joint count (0-28)                                                                                                                                                                                                                                                                                                                                                                                                                                                                                                                                                                                                                                        |         |      |         |      |                     |

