| ΔTender joint count (0-28)                                                                                                                                                                                                                                                                                                                                                                                                                                                                                                                                                                                                                                         |         |      |         |      |                     |
| ΔHAQ-DI, score (0-3)                                                                                                                                                                                                                                                                                                                                                                                                                                                                                                                                                                                                                                               |         |      |         |      |                     |
| ΔDAS28-CRP, score (0-9.4)                                                                                                                                                                                                                                                                                                                                                                                                                                                                                                                                                                                                                                          |         |      |         |      |                     |

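### The DAS28-CRP formula in Table A has no coefficient on the tender-joint term and contradicts the SAP's own 0 to 9.4 range

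*SAP*

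**What the plan says.** Table A in SAP section 6.1.3 lists the other secondary outcomes and how each is calculated. The DAS28-CRP entry applies to RA and PsA.

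- Scale: "DAS28-CRP is a composite measure of disease activity in RA ranging on a scale from 0 to 9.4".
- Inputs: "swollen and tender joint counts (SJC and TJC, 0-28), CRP (mg/L) and patient global assessment (PGA, 0-100 mm VAS". No upper limit is given for CRP.
- Equation, joint terms: "DAS28(CRP) = \sqrt{TJC} + 0.28 * \sqrt{SJC" (the closing brace follows).
- Equation, remaining terms: "0.36 * \ln(CRP + 1) + 0.014 * PGA + 0.96".

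Appendix Table 1, where the result is to be reported, repeats the scale in its row label: "ΔDAS28-CRP, score (0-9.4".

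**The concern.** The swollen-joint, CRP and patient-global terms each have a multiplier (0.28, 0.36 and 0.014). The tender-joint term has none. Either its weight really is 1, in which case the stated maximum of 9.4 should hold, or a coefficient has been left out.

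The equation is the SAP's instruction for deriving the score. If it is programmed as printed and the true weight is below 1, tender joints count for too much. The change in DAS28-CRP would then be on a scale that cannot be compared with published values, and the HFLM versus LFHM difference in that row would mostly reflect tender joints.

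**Working it through.** **Inputs.** All come from the Table A entry: TJC and SJC from 0 to 28, PGA from 0 to 100, CRP in mg/L, and a stated range of 0 to 9.4.

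**Formula as printed.** DAS28-CRP = √TJC + 0.28·√SJC + 0.36·ln(CRP + 1) + 0.014·PGA + 0.96.

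**Step 1: try to reproduce the stated maximum.** Set TJC = SJC = 28 and PGA = 100:

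- √28 = 5.292
- 0.28 × 5.292 = 1.482
- 0.014 × 100 = 1.40
- constant = 0.96
- sum before the CRP term = 9.13

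Adding 0.36·ln(CRP + 1):

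| CRP (mg/L) | Score as printed |
|---|---|
| 0 | 9.13 |
| 1.1 | 9.40 |
| 10 | 10.00 |
| 100 | 10.80 |
| 300 | 11.19 |

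The crossing point is CRP = exp[(9.4 − 9.133)/0.36] − 1 ≈ 1.1 mg/L. The 9.4 maximum is therefore not reproduced at any CRP above about 1 mg/L. CRP of 100 mg/L is a useful reference because the SAP implies it elsewhere. Appendix Table 1 gives "ΔSDAI, score (0-86"), and 86 − 28 − 28 − 10 − 10 leaves 10 mg/dl, or 100 mg/L, for CRP.

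**Step 2: the stated minimum.** With every component at zero the formula returns its constant, 0.96. A score of 0 cannot occur whatever the tender-joint weight.

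**Step 3: can the missing weight be recovered from the SAP?** Solve w·√28 + 1.482 + 0.36·ln(CRP + 1) + 1.40 + 0.96 = 9.4 for w:

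| Assumed CRP ceiling (mg/L) | w giving exactly 9.4 |
|---|---|
| 10 | 0.89 |
| 100 | 0.74 |
| 300 | 0.66 |
| 500 | 0.63 |

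The answer depends on a ceiling that the SAP does not state, so the range shows a conflict but does not identify the coefficient.

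**Step 4: size of the effect, for illustration.** Over-weighting of the tender-joint term is 1/w: 1.12-fold at w = 0.89, 1.59-fold at w = 0.63, and 1.79-fold at w = 0.56. The last weight is an assumption that is not in the SAP.

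Take a patient who goes from TJC 10, SJC 8, CRP 15, PGA 60 to TJC 3, SJC 2, CRP 5, PGA 30.

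- As printed, baseline = 3.162 + 0.792 + 0.998 + 0.840 + 0.96 = 6.75.
- As printed, follow-up = 1.732 + 0.396 + 0.645 + 0.420 + 0.96 = 4.15.
- The fall is 2.60, of which 3.162 − 1.732 = 1.43 is tender joints and 1.17 is everything else.
- With w = 0.56 the fall is 0.56 × 1.43 + 1.17 = 1.97, so the printed formula overstates it by 2.60/1.97 − 1 = 32%.
- With w = 0.89 the fall is 2.44, and with w = 0.63 it is 2.07.

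**Step 5: would a range check find it?** The patient above scores 6.75 at baseline as printed. A more active patient (TJC 20, SJC 15, CRP 30, PGA 80) scores 8.87. Both lie inside 0 to 9.4, so a range check passes them with the wrong formula in place.

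**The case against.** **The stated range may be the loose part.** The logarithm of CRP has no upper bound and the lower limit of 0 is unreachable with any tender-joint weight, so the range is not exact in any case. The breach of 9.4 above was also shown only with both joint counts and the patient global at their limits. This stands as a caution against deriving the weight from the range. It does not rescue the equation: the excess begins at about 1.1 mg/L, and the tender-joint term is still the only component without a coefficient.

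**The coefficient may have been lost in text extraction.** A leading multiplier can drop out when an equation is extracted from a PDF. This cannot be excluded, and the typeset equation should be checked first. It is unlikely, since every other coefficient survived, including the 0.28 directly after the tender-joint term.

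**The outcome is minor.** This stands. DAS28-CRP is not a component of ACR20 as defined in section 6.1.1, and it is not among the key secondary outcomes in section 6.1.2. It is therefore outside the Hochberg procedure in section 4.1. Appendix Table 1 reports it as a difference with a 95% CI and has no P value column.

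**A stronger reading is tempting.** A reader might infer that Table A also has the PASI weights wrong, because it gives "the head: 10% of total body, the trunk: 20%, the upper extremities: 30% and the lower extremities: 40"%, with the arms above the trunk. That would reach the primary outcome through PASI 75, since section 6.1.1 says: "For the measurement and calculation of HBI, Mayo Clinic Score and PASI see table A". The SAP does not support this. The printed weights sum to 100% and give 12 × 6 × 1.00 = 72, which is the stated maximum. Exchanging the two figures also gives 72, and no other part of the SAP gives different weights. Calling them transposed would rest on outside knowledge alone.

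**Conclusion.** The point holds for DAS28-CRP from the SAP alone. The printed equation has an unweighted tender-joint term and cannot be reconciled with the 0 to 9.4 scale given in Table A and Appendix Table 1. At the joint and patient-global limits it runs from 9.13 at CRP 0 to 10.8 at 100 mg/L, and its floor is 0.96.

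The correct coefficient cannot be derived from the SAP. The 1.79-fold and 32% figures hold only if it is 0.56. The direction, over-weighting of tender joints, holds for any true weight below 1.

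The consequence is confined to the change in DAS28-CRP for RA and PsA. The constant of 0.96 cancels in a change score, so the wrong lower limit is a labelling matter. The primary outcome, including ACR20 and PASI 75, and the key secondary outcomes are not affected. This is a clear error that is cheap to correct before analysis, but it does not threaten the study's main conclusions.

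**What to change.** 1. Look at the typeset equation in the source PDF to confirm that the tender-joint coefficient is absent there too.
2. If it is, take the coefficient from reference 41, which the SAP cites for this formula, and insert it in Table A.
3. Correct the stated range in Table A and the row label in Appendix Table 1. The lower limit is 0.96 for the equation as given. An upper limit is meaningful only with the CRP value that it assumes.
4. Check the derivation code against the cited formula term by term, or recompute a few patients by hand. A check that scores fall within range is not enough, because typical patients stay inside it with the wrong weight.

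The cost is one equation, two range statements and a short code check. No data collection, analysis model or sample size changes.

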#### 6.1.4. Exposure and confounding variables

##### **Exposure variable**

We will stratify the patients in BELIEVE into two groups (exposed versus unexposed) based on the ratio of fiber to meat intake (FtM [grams per day]):

$$FtM = \frac{\text{Fibers}}{\text{Red and processed meat}},$$

which will be calculated from the food frequency questionnaire (FFQ) administered to the patients at baseline. From this ratio, exposure is defined as the upper 33.3% of the total study sample (called the high fiber low meat group, HFLM) leaving the lower 66.6% of the sample as those un-exposed (low fiber high meat, LFHM).

Secondary explorative analysis will include defining exposure as 1) the upper 33.3% (high fiber; HF) of the study sample with respect to intake of dietary fibers (versus the lower 66.6% [low fiber; LF], and 2) the lower 33.3% (low meat; LM) of the study sample with regard to red/processed meat intake (versus the upper 66.6% [high meat; HM]).

The FFQ used in the present study was developed and validated in relation to the 2007-2008 Danish Health Examination Survey [47]. It was internet-based and administered to the participants prior to initiation of biological therapy with questions covering the habitual dietary intake during the past month. The FFQ contained information from 267 different food groups. For each item, frequency of consumption was evaluated by eight categories ranging from “newer/seldom” to “twice or more per day”. In order to quantify portion sizes for main meals and other main food items, a photographic food atlas consisting of different food and meal series was included at the end of the questionnaire. However, fixed portion sizes were used for some food items with more standardized portion sizes such as fruits. The actual weight in grams for each food item will be derived by multiplying the reported frequency of consumption with estimated portion sizes. Total energy intake and intake of different nutrients will be quantified using the Danish Food Composition Tables (National Food Institute, Technical University of Denmark, <https://frida.fooddata.dk/>).

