**Nutrition**

Energy, mean (SD), kJ/d  
Fibre, mean (SD), g/d  
Red/processed meat, mean (SD), g/d

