| Serious adverse events (SAEs), n (%)                                                                                                                                                                                                                                                                                                                                                                                                                                                                                                                                                                                                                                                                                                                                                                                                                                                                                                                                         |    |    |                     | n.a.                        |                     | n.a.                                   |                     | n.a.     |
| * Key secondary outcomes are interpreted by the Benjamini Hochberg approach. Adjusted for CID type. Adjusted for CID type, age, sex, clinical center, smoking and meat intake. Adjusted for CID type, age, sex, clinical center, smoking, meat intake and propensity score. HF; High fiber (upper 33.3% of the study sample with regard to fiber intake), LF; Low fiber (lower 66.6% of the study sample with regard to fiber intake), CI; confidence interval, HBI; Harvey Bradshaw Index, Mayo; Mayo Clinic Score, ACR20; 20% improvement according to the criteria of the American College of Rheumatology, ASAS20; 20% improvement according to Assessment of Spondyloarthritis International Society, PASI75; 75% improvement in the Psoriasis Area and Severity Index, CRP; C-reactive protein, VAS; visual analog scale, SF-12; 12-item Short Form survey, PCS; physical component summary, MCS; mental component summary. |    |    |                     |                             |                     |                                        |                     |          |

Appendix Table 4. Secondary explorative analyses; comparison of low vs. high red/processed meat intake.

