\*Key secondary outcomes are interpreted based on the Benjamini Hochberg approach. Adjusted for CID type. Adjusted for CID type, age, sex, smoking, clinical center, and fiber intake. Adjusted for CID type, age, sex, smoking, clinical center, fiber intake, and propensity score. LM; Low meat (lower 33.3 % of the study sample with regard to red/processed meat intake), HM; High meat (upper 66.6% of the study sample with regard to red/processed meat intake), CI; confidence interval, HBI; Harvey Bradshaw Index, Mayo; Mayo Clinic Score, ACR20; 20% improvement according to the criteria of the American College of Rheumatology, ASAS20; 20% improvement according to Assessment of Spondyloarthritis International Society, PASI75; 75% improvement in the Psoriasis Area and Severity Index, CRP; C-reactive protein, VAS; visual analog scale, SF-12; 12-item Short Form survey, PCS; physical component summary, MCS; mental component summary.

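### The exploratory high-fibre and low-meat contrasts rank patients on unscaled grams per day and no specified model includes total energy, so they can be biased in opposite directions if energy intake is related to response.

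*SAP*

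**What the plan says.** SAP 6.1.4 (Exposure variable) sets up three dietary contrasts.

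- **Primary.** Patients are split "based on the ratio of fiber to meat intake (FtM [grams per day"]), with the upper third as the exposed group (HFLM) and the rest as unexposed (LFHM).
- **Exploratory, fibre (HF vs LF).** The exposed group is "the upper 33.3% (high fiber; HF) of the study sample with respect to intake of dietary fibers".
- **Exploratory, meat (LM vs HM).** The exposed group is "the lower 33.3% (low meat; LM) of the study sample with regard to red/processed meat intake".

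Grams are obtained as reported frequency times portion size. The nutrition block of Table 1 uses the same scale: "Fibre, mean (SD), g/d" and "Red/processed meat, mean (SD), g/d". No density, residual or per-MJ form is defined for HF or LM.

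Energy is available from the same questionnaire ("Total energy intake and intake of different nutrients will be quantified using the Danish Food Composition Tables") and has its own row in Table 1. It is in none of the specified covariate sets:

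- The confounders named in 6.1.4 are sex, age and smoking. CID type and clinical center are the other adjusting variables.
- The adjusted fibre model, per the Appendix Table 3 footnote, is "Adjusted for CID type, age, sex, clinical center, smoking and meat intake".
- The adjusted meat model, per the Appendix Table 4 footnote, is "Adjusted for CID type, age, sex, smoking, clinical center, and fiber intake".
- The third model in each table adds only the propensity score.
- The fibre-by-meat interaction in 6.2 uses the same covariates.

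The Table 1 footnote has a data-driven rule that flags any variable with a standardised mean difference (SMD) above 0.5. Its group columns are HFLM and LFHM only.

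**The concern.** Grams of fibre and grams of meat can both be expected to rise with how much a person eats. Dividing one by the other removes much of that common part, so the primary contrast has some built-in protection. The two single-food contrasts do not. Ranking high on fibre tends to pick larger eaters and ranking low on meat tends to pick smaller eaters. Any link between total intake and response then pushes the two contrasts in opposite directions.

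These models address additional hypotheses 1 and 2 in section 2.4 (independent associations of low meat and high fibre) and both exploratory secondary objectives in 2.5. The same groups form the interaction test. At stake is whether an apparent fibre or meat association reflects that food or the quantity eaten. The one screening rule in the plan that could bring energy into a model is not applied to these contrasts.

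**Working it through.** The SAP gives no figure on this point. Its power figure of 0.924 (3.2: 318 patients split 106 and 212, 60% vs 40%, two-sided 0.05) reproduces as 0.9245, but it does not bear on this issue.

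**Step 1: imbalance by construction.** For a standard normal variable, the upper third starts at z = 0.431, where the density is 0.364. The mean difference between the upper third and the rest is 0.364/(1/3) + 0.364/(2/3) = 1.636 SD. If a food correlates r with energy, the energy difference is 1.636 × r: 0.49 SD at r = 0.3 and 1.15 SD at r = 0.7. Divided by the smaller within-group SD, this gives an SMD of about 0.5 to 1.4.

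**Step 2: simulation under no diet effect.** There were 400,000 patients per scenario. All inputs below are assumptions, since the SAP gives none:

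- correlation of log fibre and log meat with energy 0.3 to 0.7;
- log-SD 0.4 for fibre and 0.6 for meat;
- 50% response at mean energy;
- response depends on energy alone, with an odds ratio (OR) per SD of 1.0, 1.25, 1.5 or 1/1.5.

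The HF model was adjusted for meat and the LM model for fibre, as planned. Age, smoking, CID type and center were not simulated.

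| r fibre / r meat | Energy SMD: HF, LM, ratio | HF and LM OR, energy OR 1.25 | energy OR 1.5 | energy OR 1/1.5 |
|---|---|---|---|---|
| 0.3 / 0.3 | 0.51, −0.51, −0.15 | 1.10, 0.90 | 1.20, 0.84 | 0.84, 1.19 |
| 0.5 / 0.5 | 0.89, −0.89, −0.26 | 1.15, 0.86 | 1.31, 0.78 | 0.78, 1.29 |
| 0.6 / 0.4 | 1.12, −0.69, 0.00 | 1.20, 0.91 | 1.42, 0.83 | 0.70, 1.19 |
| 0.7 / 0.5 | 1.38, −0.89, −0.05 | 1.24, 0.90 | 1.47, 0.83 | 0.68, 1.23 |
| 0.7 / 0.7 | 1.37, −1.38, −0.44 | 1.18, 0.84 | 1.36, 0.74 | 0.75, 1.36 |

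With an energy OR of 1.0, the HF and LM ORs were 0.99 to 1.01 in every row.

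**Step 3: adjusting for sex.** With men assumed 0.8 SD higher in energy, correlations of 0.4 to 0.7, and both sex and the other food in the model:

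- energy OR 1.25: HF 1.13 to 1.18, LM 0.87 to 0.90;
- energy OR 1.5: HF 1.21 to 1.32, LM 0.77 to 0.83;
- energy OR 1/1.5: HF 0.76 to 0.82, LM 1.21 to 1.31.

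The attenuation is modest.

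**Step 4: does the screening rule catch it?** For the ratio groups, the only ones the rule compares, the energy SMD was at most 0.44 in size, below 0.5 throughout. For HF and LM it was about 0.5 or more throughout, but the rule is not applied to them.

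**Step 5: the primary contrast.** The unadjusted OR for the ratio groups was 0.91 to 1.00 at an energy OR of 1.25 and 0.84 to 1.00 at 1.5. The furthest value came from the 0.7 / 0.7 row.

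**Step 6: size against precision.** With 106 and 212 patients and 50% response, the standard error of the log OR is √(1/53 + 1/53 + 1/106 + 1/106) = 0.238. The 95% CI factor is exp(1.96 × 0.238) = 1.59. A spurious HF OR of 1.10 to 1.47 is ln 1.10/0.238 = 0.4 to ln 1.47/0.238 = 1.6 standard errors.

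**The case against.** **Bias is not established.** A reader might infer that the two contrasts are biased, with fibre made to look protective and low meat harmful. The SAP does not support that. It says nothing about whether energy intake is related to response given the covariates. With no relation there is no bias, and with an inverse relation the signs reverse. This objection stands, and the point is conditional for that reason.

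**The disease-activity explanation is unsourced.** A reader might suppose that active disease lowers intake over the past month and so fixes the direction. The SAP does not say so. It pools six diseases, with remission thresholds for CD and UC and relative improvement for the others, so the sign against the pooled endpoint would be undetermined even then. This also stands.

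**Energy would not be a full cure.** In the simulation behind the table, adding energy returned both ORs to 0.99 to 1.01, but only because response was made to depend on energy alone, measured without error. In a further simulation with assumed values, disease activity drove response, lowered energy and also directly lowered fibre. There the null HF OR was 1.28 to 1.43 without energy and still 1.15 to 1.32 with it.

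**The question changes.** The stated aim is prognostic and the hypotheses concern intake. Meat contributes to energy, and 6.1.4 excludes covariates that are effects of the exposure. Conditioning on energy asks about a food at a given total intake, not about the amount eaten. That is a real choice to be stated, but the plan does not discuss it.

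**Scope.** Only analyses labelled exploratory are affected. This is correct and limits the weight of the point. None of these objections alters the text: a computed variable likely to be imbalanced by construction is outside the models meant to separate fibre from meat.

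**Conclusion.** The point holds in conditional form, as an inexpensive improvement to the exploratory analyses. HF/LF and LM/HM rank patients on unscaled intake, energy is in no specified model, and the SMD rule looks at a different contrast. If energy is related to response given the covariates, the two contrasts can be biased in opposite directions, with a sign the SAP does not determine.

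Under the stated assumptions, the spurious HF OR runs from about 1.10 to 1.47 and the LM OR from 0.74 to 0.91 for an energy OR of 1.25 to 1.5 per SD. At 1/1.5 they are 0.68 to 0.84 and 1.19 to 1.36, and at 1.0 there is no bias. Against the sampling error this is small at the low end and not negligible at the high end. Adjusting for the other food and sex reduces it without removing it.

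A reader might extend this to the primary result. The working does not support that as a general conclusion: the ratio largely cancels energy, with appreciable residue only in the most extreme scenario.

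**What to change.** In SAP 6.2 and the footnotes of Appendix Tables 3 and 4, add total energy intake (kJ/day, continuous) to the adjusted and propensity models for HF/LF, LM/HM and their interaction. Report the energy SMD for HF vs LF and for LM vs HM beside those results, since Table 1 will not show it.

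State in 6.2 that these estimates then refer to fibre or meat at a given energy intake and no longer to the amount eaten. Do not claim that all bias is removed, because energy is at best a partial proxy for disease activity.

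The cost is 1 df per model and that change of interpretation. The covariate is already to be computed, and no new data are needed.
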